### Qualitative Phase: Study Instrument and Interview Session

A small sample of participants was invited to participate in the qualitative phase, with an equal number of samples from each SAC. As described by previous scholars, 10% of the computed sample size for the quantitative phase was recruited for the interview session. However, an equal number of older individuals were selected from each SAC in various parts of Singapore to participate in the study. The interview session was performed using a semistructured questionnaire. The instrument enables participants to share their views and experiences of counseling services, while some of the responses can be measured numerically.

Six components were explored during the interview session, including the use of the Advanced Care Planning (ACP) booklet among older people, the Trait Meta Mood Scale (TMMS), older people’s accessibility and receptiveness toward counseling, and the improvement of older people’s dignity in emotional management and decision-making. The interview guide was reviewed in subsequent sessions to explore any new emerging themes.

### Quantitative Phase: Instrument Development and Administration

This study uses the ACP and the TMMS instruments. The ACP is a booklet that was designed by the Agency for Integrated Care for recording and planning health and personal care. It comprises 5 main sections that focus on important lifestyle activities, concerns about current health status, views toward life and health, end of life, and preferred end-of-life care. The items are presented as either multichoice options or on a 5-point Likert scale ranging from 1 to 5, depending on the section. For the section on lifestyle activities (4 items), 1=“there is little point in being alive without the quality of life,” while 5=“I would like to be able to live for as long as possible.” For the section on participants’ views toward end of life (4 items), 1=“strongly disagree” and 5=“strongly agree.” On the other hand, the section on preferred end-of-life care is presented as multichoice options with 9 items.

Meanwhile, the TMMS is a 24-item instrument that was developed to measure meta-mood experience [29]. The TMMS is considered suitable for this study as it is the most used self-administered measurement for individuals’ emotional management [29]. The instrument comprises 3 subscales (Attention to Feelings, Clarity of Feelings, and Mood Repair) with 8 items each that evaluate the 3 meta-mood experience components with a 5-point Likert scale ranging from 1=“strongly disagree” to 5=“strongly agree.” The Attention to Feelings Subscale measures attention to personal and external moods and emotions; the Clarity of Feelings Subscale assesses personal abilities to discriminate feelings among one another; and the Mood Repair Subscale evaluates older individuals’ ability to perform self and external regulations [30].

A structured questionnaire was also developed to assess participants’ views regarding counseling and its impact on their dignity and decision-making process. This was based on the themes identified in the qualitative study and an in-depth review of several studies in the literature. Operational definitions were also developed based on the themes obtained. Three experts assessed the questionnaire for content validity. Thereafter, the instrument was distributed to 10 social workers or counselors for face validity assessment. The comments received were reviewed and necessary modifications were made. The final questionnaire was presented in English, and no translation into local languages was conducted. Pretesting was performed on 20 older individuals from selected SACs for internal consistency and reliability. Findings from the experts’ opinions and pilot testing were used to prevent potential ceiling and floor effects from the questionnaire items that may affect accurate data interpretation. The developed questionnaire was distributed to randomly selected older individuals at all selected SACs. The data obtained from the quantitative and qualitative approaches were combined to provide a more robust assessment of the study. Table 1 depicts the research matrix.

**Table 1 table1:** Research matrix.

Research objectives	Quantitative	Qualitative
To assess advance care planning among older people and their perception of life and health, end of life, and end-of-life care	✓	✓
To explore older people’s accessibility and receptiveness toward counseling		✓
To elucidate older people’s perspectives on counseling and its impact on emotional management and decision-making		✓
To assess older people’s competencies in emotional management	✓	
To propose an intervention model for enhancing older people’s well-being and dignity through psychological counseling	✓	✓

### Ethical Considerations

Ethical considerations in this study entail 2 key ethical principles: honesty and respect for human rights [27,31-33]. Certain ethical questions need to be addressed, since older individuals are research participants. The privacy, safety, and confidentiality of participants’ data are guaranteed. Hence, both informed and signed consent were obtained before the interview and questionnaire administration. A cover letter with vital information on the research objectives was attached to the questionnaire and interview guide. This study protocol has been approved by the Universiti Sains Malaysia Human Research Ethics Committee (USM/JEPeM/21110760).

### Management

Participants’ anonymity will be protected in this study [34-36]. Data will be kept confidential to ensure that the identities of older individuals are protected [37-39]. Research instruments and clinical records containing participants’ data will be represented in a coding system. Thus, participants’ private information will not be revealed when submitting the data and findings to regulatory institutions or sponsors [40,41]. Only the researchers will be able to access the participants’ records and the coding system. Two copies of consent forms were provided to be signed by the researcher and each participant. All the files will be stored in a single folder in a secured location.

This research poses no risk to the participants. No personal expenses will be incurred by the participants during the study. Furthermore, no incentives or financial compensation will be given for participation. The research budget will be used for any further expenses. This study is based on voluntary participation and has no implications for the participants’ counseling if they decide not to participate. Older individuals can decide to withdraw from the research regardless of time, if desired, without any consequences to their counseling or care at the SACs. The expected research findings might be published in a journal article or presented at conferences or meetings; however, participants’ identities will remain confidential.

### Quality Control Measures

A number of methodological resources, such as mixed method study design, inclusion criteria, and random sampling, were used in this study to minimize bias and ensure quality data collection. The interview session was performed by the principal researcher, while trained enumerators assisted in the quantitative phase of data collection. The enumerators were trained during the pilot test to familiarize them with the research instrument. To further ensure quality control, the principal researcher assessed the enumerators periodically to see if they were following the survey protocol. If necessary, the enumerators also assisted the participants while they completed the questionnaire to minimize missing data. Quality control was assessed in the retrieved questionnaires based on the quality and completeness of the data.

### Data Analysis

Findings from the qualitative study will be transcribed and coded. Interview transcripts will be analyzed using NVivo (version 12; QSR International). The identification, coding, and categorization of meaningful patterns into themes and subthemes will be performed to facilitate the construction of a structured questionnaire for the quantitative study. For the quantitative phase, the internal consistency of the questionnaire items will be evaluated using a reliability test based on Cronbach α values. Items will be considered acceptable and reliable if the Cronbach α value is equal to or greater than .7. Participants’ background information and other sections in the questionnaire will be analyzed using descriptive statistics. Continuous variables will be subjected to normality tests using the Smirnov-Kolmogorov test and presented as means (SD) or medians (IQR) accordingly. Statistical tests such as a 2-tailed, 1-sample *t* test or Wilcoxon signed rank test will be applied. A *P* value of .05 will be considered statistically significant, and all empirical analyses will be performed using SPSS (version 25; IBM Corp). The flow of the research process, including the vital concepts, is presented in Figure 1.

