**Methods:**

A mixed method study design involving quantitative and qualitative methods will be used. Older individuals receiving some form of preventive, primary, or long-term care in the community through voluntary welfare organizations from the senior activity centers located in eastern Singapore participated in the qualitative phase. Six older individuals from each senior activity center have been enrolled for the interview phase to explore 6 components: the Advanced Care Planning (ACP) booklet, Trait Meta Mood Scale (TMMS), accessibility and receptiveness toward counseling, and emotional management and decision-making. The ACP, an instrument designed to assess advanced care planning among older individuals, and the TMMS, an instrument developed to measure meta-mood experience and emotional management, were used in the quantitative phase among 100 participants. The data will be analyzed thematically using NVivo version 12, whereas descriptive statistics and a 2-tailed, 1-sample *t* test will be conducted in SPSS (version 25; IBM Corp) for empirical data analyses.

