### Research Objectives

The objectives of this study are as follows: (1) to explore older people’s accessibility and receptiveness toward counselling; (2) to assess the improvement of older people’s dignity in emotional management and decision-making processes following psychological counseling; and (3) to propose an intervention model for enhancing older people’s well-being through psychological counseling.

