### Research Questions

Due to the paucity of data regarding the impact of counseling services on older adults’ dignity and the aging process, this study aims to answer the following questions:

Do older people in Singapore have counseling access and receptiveness?Do counseling services improve emotional management among older people?Do counseling services improve dignity among older people?Do counseling services affect decision-making processes among older people in Singapore?

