In terms of the impact of counseling on emotional management and decision-making, diverse views ranging from positive to negative effects may be conveyed by participants since they might have faced challenges in seeking counseling assistance. For instance, a previous study conducted in Tehran, Iran, found that psychological counseling on mental well-being had a positive impact on emotion and self-management ability among older women [57]. Dai et al [58] also performed a meta-analysis of studies conducted among Chinese populations and found that psychologically based therapies were effective in ameliorating depression symptoms among older people. The contents of the ACP instrument used in this study entailed pertinent topics on mental health, the selection of treatment goals (comfort-focused vs full treatment), available care options in the community, and available care options during end of life, which might have a positive effect on emotional management and decision-making. However, difficulties in assessing counseling services or challenges are faced during the counseling process.

The fourth objective of this study emphasized participants’ competencies in emotional management after counseling assistance. This objective will entail both a semistructured interview and a quantitative analysis by using the TMMS, which focuses on participants’ attention (perceived attention paid to personal emotional conditions), clarity (perceived understanding of personal emotional conditions), and repair (perceived ability to regulate personal emotional conditions). The TMMS is one of the most commonly used self-administered measurements for perceived emotional competence in older people [29]. It provides the opportunity to bridge current empirical gaps on emotions and to elucidate developmental trajectories throughout a person’s life span. Based on the alignment between the ACP contents and items in the TMMS, as well as findings from previous local studies on the impact of counseling [20], we expect older people’s competencies in emotional management and decision-making to improve after seeking counseling assistance. Results from this study may assist policymakers in deploying strategies to promote mood repair and emotional management in the Singaporean aging population to improve their receptiveness toward counseling interventions.

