### Strengths and Limitations

Given the paucity of research on counseling as an intervention to enhance older people’s dignity within the community, this study has attempted to fill in the research gap between counseling and Singaporean government policy on aging in place, thus adding to the current body of knowledge and literature in the research area both at local and global levels. The variables and specific events investigated in this study, such as receptiveness and accessibility to counseling centers, improved emotional management and decision-making, and quantitative assessment of perceived attention, clarity, and mood repair among older individuals, represent the novelty of this research. To date, only a few studies have considered the lived experiences and interactions of older adults with counselors or social workers. This study represents the first attempt to use mixed research methods to bridge the research gap. This combined approach will facilitate the collection of vital data through in-depth interviews and survey methods to elucidate older individuals’ lived experiences and interactions with qualified and Singapore Association of Counseling and Singapore Association of Social Workers–accredited counselors or social workers.

However, the study design enabled the recruitment of participants with similar characteristics, and the inclusion and exclusion criteria used in selecting the study participants might have excluded older individuals with pertinent information on the research topics. Furthermore, the use of semistructured interview sessions also has its limitations, as respondents might be unwilling to provide in-depth information to the questions being asked. Moreover, the ACP instrument used in the qualitative phase has some closed-ended questions in which participants were not free to express their opinions. This might contribute to a degree of response bias. Last, this study has a cross-sectional design, and the findings will only reveal the association between the studied variables, such as accessibility and receptiveness toward counseling, perspectives on dignity and barriers to counseling assistance, and the related impact on emotional management and decision-making. In other words, no causal relationships can be inferred. Longitudinal, prospective, and randomized control study designs are more likely to generate the required data to infer causal effects and relationships between the studied concepts.

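### Objective 2, research questions 2 to 4 and the expected finding speak of improvement or an effect after counseling, which one-sample tests on a single cross-sectional measurement cannot show

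*Protocol article*

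**What the plan says.** **Aim.** In the Protocol article, objective 2 under Research Objectives is "to assess the improvement of older people’s dignity in emotional management and decision-making processes following psychological counseling". Under Research Questions, question 2 is "Do counseling services improve emotional management among older people"; question 3 asks the same about dignity, and question 4 asks about an effect on decision-making. Expected Findings ties the aim to the TMMS. It says "The fourth objective of this study emphasized participants’ competencies in emotional management after counseling assistance", names the TMMS as the quantitative tool for that objective, and adds "we expect older people’s competencies in emotional management and decision-making to improve after seeking counseling assistance".

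**Weaker wording elsewhere.** The abstract's Objective and Table 1 (the research matrix) list five objectives, and none mentions improvement following counseling. The TMMS objective there is to assess competencies in emotional management, marked quantitative only. Perspectives on counseling and its impact are marked qualitative only.

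**Design.** Results describes one face-to-face administration of the Advanced Care Planning booklet and the TMMS. It began on March 22, 2022, closed on May 10, 2022, and involved 100 consenting participants. Strengths and Limitations states that "this study has a cross-sectional design, and the findings will only reveal the association between the studied variables" and that causal relationships cannot be inferred.

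**Analysis.** The abstract says "descriptive statistics and a 2-tailed, 1-sample *t* test will be conducted in SPSS". Data Analysis says "Statistical tests such as a 2-tailed, 1-sample *t* test or Wilcoxon signed rank test will be applied", with a significance level of .05. Neither place names the variable to be tested or the value it is tested against.

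**The concern.** Improvement is a change from an earlier state, or a difference from what would have been seen without counseling. Showing it needs a second measurement or a comparator, and the article describes neither. The named tests therefore answer a different question: whether the sample mean or median differs from a chosen constant.

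The Implications and Conclusion sections direct the findings to policymakers, for standardizing training and counseling content and for implementing a model. A significant TMMS result, set beside the stated expectation of improvement, would invite the conclusion that counseling improved emotional management. The data could not support that conclusion.

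**Working it through.** The article gives no numerical result on this point to reproduce, so the check compares its statements and then illustrates the consequence.

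**1. What each part requires or supplies**

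| Section | What it requires or supplies |
|---|---|
| Research Objectives (2); Research Questions (2 to 4); Expected Findings | A change after, or an effect of, counseling |
| Abstract Objective; Table 1 | Level of competency (TMMS); impact of counseling from interviews |
| Results; Strengths and Limitations | One measurement per person; associations only |
| Abstract Methods; Data Analysis | One-sample *t* or Wilcoxon signed rank test, no reference value |

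The first row asks for more than the other three can deliver. The last row also falls short of the third: an association needs two variables, and a one-sample test uses one.

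**2. What the test measures**

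The statistic is t = (mean − c) / (s/√n), where c is the reference constant. Counseling status does not enter it. The Wilcoxon signed rank test can be used on paired data, but no second measurement is described to pair. Here it is only the nonparametric counterpart of the same comparison.

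**3. Illustration**

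Inputs from the article: n = 100, two-sided 5% level, items scored 1 to 5. Assumed, because the article gives no values: c = 3 (midpoint of the item-mean scale), SD 0.7 to 0.8, and a counseling effect of exactly zero. The noncentrality is δ = (μ − 3)/(SD/√100), and the critical value of *t* with 99 degrees of freedom is about 1.984.

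| True mean μ | SD | δ | P(significant) |
|---|---|---|---|
| 3.3 | 0.8 | 0.3/0.08 = 3.75 | 0.960 |
| 3.3 | 0.7 | 0.3/0.07 = 4.29 | 0.989 |
| 3.2 | 0.8 | 0.2/0.08 = 2.50 | 0.697 |
| 3.2 | 0.7 | 0.2/0.07 = 2.86 | 0.808 |

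With SD from 1.0 down to 0.6, a mean of 3.3 gives 0.844 to 0.999.

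The converse also holds. Suppose counseling truly raised the mean from 2.7 to 3.0. The observed mean then sits at c, δ = 0, and the test is significant with probability 0.05. The result follows the distance from c, not improvement, and a larger sample would not change that.

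**4. A contrast by counseling history**

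If prior counseling had been recorded, the detectable difference in SD units would be about (1.96 + 1.28) × √(1/n₁ + 1/n₂) at 90% power.

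- 50/50 split: 3.24 × 0.200 = 0.65 (exact *t* calculation 0.655).
- 30/70 split: 3.24 × 0.218 = 0.71 (exact 0.714).

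Both splits are assumed. The 30% in the sample size section concerns access and receptiveness, not counseling history.

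**The case against.** - **The abstract and Table 1 do not claim improvement.** This stands and narrows the point. On that matrix, a one-sample test describing competency level is not assigned to show change. But Expected Findings attaches the TMMS to competencies after counseling and predicts improvement, so the matrix does not rescue the plan. It shows that the article disagrees with itself about its objectives.
- **Impact of counseling is also collected quantitatively.** A structured questionnaire on views of counseling and its impact on dignity and decision-making is described under the quantitative instruments. A reader might infer that research questions 2 to 4 get no quantitative information at all, and that would be too strong. The questionnaire and interviews can record perceived impact. They cannot record measured improvement.
- **The list of tests is open, and a fuller plan may exist.** This is fair: it cannot be said that these are the only tests, or that no meaningful reference value exists, only that none is stated. But no further test or analysis plan can add a baseline to data collection that closed on May 10, 2022.
- **The causal limitation is admitted.** It is, and that makes misreading less likely. It also contradicts the objective, questions and expectation left in place.
- **Whether counseling is given.** A reader might infer that the study provides none. The documents do not settle this: the inclusion criteria require willingness to attend counseling sessions, and the Management section refers to participants' counseling or care at the centers. The point does not depend on the answer, because no before-and-after or between-group measurement is described either way.

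**Conclusion.** The point holds as a mismatch between the stated aim and what the described design and named tests can show, together with an inconsistency among the article's own statements of its objectives. Objective 2, research questions 2 to 4 and the expected finding cannot be answered as measured improvement or effect. The named tests also do not estimate the association that Strengths and Limitations promises.

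This conclusion is structural and rests on the text alone. The rejection rates (96% to 99% at a mean of 3.3 and 70% to 81% at 3.2, with no counseling effect) depend on the assumed reference of 3 and SD of 0.7 to 0.8. They illustrate the problem and are not predictions for this study. That the authors will claim improvement from a one-sample result is a risk created by the wording, not something the article says it will do.

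**What to change.** 1. Reword objective 2, research questions 2 to 4 and the expectation in Expected Findings to match the abstract, Table 1 and Strengths and Limitations: current competencies in emotional management, and perceived impact of counseling.
2. State that no TMMS result will be interpreted as improvement after, or an effect of, counseling.
3. Report TMMS subscale means with 95% CIs as the main quantitative result. With n = 100 and the assumed SD of 0.7 to 0.8, the half-width is 1.984 × SD/10, or 0.14 to 0.16 on the item-mean scale. Keep a one-sample test only against a stated reference value, as a description of competency level.
4. Optionally, if counseling history was recorded (the article does not say that it was), compare TMMS subscales by prior counseling. Report this as an exploratory association confounded by the reasons people sought counseling. By the calculation above, only fairly large differences would be detected with 90% power.

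The first three steps change wording and reporting only and need no new participants or data. The cost is a more modest claim.
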